**Protocol Synopsis**

**Title of Study:** Randomized controlled Single blinded prospective multi centre clinical trial to investigate the safety and efficacy of ZingiVir-H as an adjuvant therapy in hospitalized adults diagnosed with coronavirus disease 2019 (COVID-19).

**Name of Sponsor/Company:** Pankajakasthuri Herbal Research Foundation, Thiruvananthapuram, Kerala, India

**Name of Investigational Product:** ZingiVir-H

**Name of Active Ingredient:** Herbal ingredient extracted from Lavanga (*Eugenia caryophyllus*), Ardraka (*Zingiber officianale*), Mustha (*Cyperus rotundus*), Parpataka (*Hedyotis corymbosa*), Ajamoda (*Trachyspermum ammi*), Hingula (Cinnabar, HgS), Haratala (Arsenic trisulphide)

**Objectives**

**Primary:**

- The primary objective of this study is to evaluate the efficacy of ZingiVir-H regimens and standard of care compared to placebo and standard of care (SOC), with respect to clinical status assessed based on patient diary data and based on Ordinal scale on the ratio of improvement. [Time Frame: From the time of randomization until the time of alleviation of all symptoms, assessed up to the test results shows negative]
- To determine the safety of ZingiVir-H in this test population.

**Secondary:**

- Time to a normal body temperature [ Time Frame: From the time of randomization until the time of normal body temperature, assessed up to 15 days]
- Time to the alleviation of nasal/throat/chest symptoms [ Time Frame: From the time of randomization until the time of absence of nasal/throat/chest symptoms, assessed up to 15 days
- Proportion of participants in each group with normalization of fever [ Time Frame: day 7 and day 15 ]
- Proportion of participants in each group with oxygen saturation > 94% on room air for >24h [ Time Frame: day 7 and day 15 ]
- Time to fever normalization (if febrile at baseline) [ Time Frame: within 15 days ]
- Time to first negative SARS-CoV-2 PCR in NP swap (if pos. at baseline) [ Time Frame: within 15 days ]
- Time to first negative SARS-CoV-2 PCR in lower respiratory tract specimens (sputum, bronchoalveolar lavage, tracheal aspirate) (if positive at baseline) [ Time Frame: within 15 days ]
- Duration of oxygen therapy [ Time Frame: within 30 days ]
- Proportion of participants in each group with need for mechanical ventilation [ Time Frame: within 30 days ]
- Duration of hospitalization [ Time Frame: within 28 days ]
- All cause mortality [ Time Frame: day 30 ]

**Study Center(s):** Study in Indian population and recruitment will happen up to 5 research sites based on competitive patient recruitment.

**Phase of Development:** Proof of Concept/ Intervention Trial on traditional medical product.

**Study Period:**

Estimated time of first subject enrollment: 1 Q 2020

Estimated time of last subject enrollment: 1Q 2020

Number of Subjects (planned): Approximately 112 randomized subjects with assumed drop-outs of 10%; 100 evaluable subjects.

**Diagnosis and Main Criteria for Inclusion of Study Subjects:**

This study targets infectious subjects normally associated with treatment in hospital setting. The following main criteria for inclusion must be met for study entry:

- Patients of both sexes aged from 18 years to 60 years old.
- Willing and able to provide written informed consent prior to performing study procedures by the subject or legal guardian willing and able to provide written informed consent prior to performing study procedures
- Patients with Severe Acute Respiratory Syndrome Coronavirus (SARS-CoV)-2 infection confirmed by RT Polymerase chain reaction (RT-PCR) test between 1 and 120 Hours before randomization
- Currently hospitalized and requiring medical care for COVID-19
- Peripheral capillary oxygen saturation (SpO2) > 94% on room air at screening
- Radiographic evidence of pulmonary infiltrates

**Investigational Product, manufacturing, Dosage and Mode of Administration:**

The study drug ZingiVir-H is a poly herbo-mineral formulation, which is a blend of antiviral phyto-molecules and processed purified and detoxified form of natural metallic compounds. It is a unique combination of Lavanga (Eugenia caryophyllus), Ardraka (Zingiber officianale), Mustha (Cyperus rotundus), Parpataka (Hedyotis corymbosa), Ajamoda (Trachyspermum ammi), Hingula (Cinnabar, HgS), Haratala (Arsenic trisulphide) and Pharmaceutical grade starch. Even though the study drug contains minerals such as HgS and As2S3 their dose is designed in such a way that there is no cumulative dose sufficient for making any type of toxicity in the continuous usage for maximum of 15 days. The drugs in the combination have showed marked antiviral, antipyretic and immunomodulatory effects.

**Therapeutic dose**:

ONE tablet (500 mg) each consumed once in 3 hours ±1 hour between 6 AM and 9 PM in a given day (6AM, 9AM, 12Noon, 3PM, 6PM, 9PM) for a minimum duration of 10 days to Maximum 15 days as per the clinical conditions and disease outcome.

**Masking:**

Quadruple (Participant, Care Provider, Investigator, Outcomes Assessor)

**Duration of Treatment**: Fifteen (15) days of study drug regimen and a follow-up on 30^th^ day

**Reference Therapy, Dosage and Mode of Administration**: Placebo and Standard of Care (SOC)

Placebo for this study is supplied as identically labeled, tablets. Placebo will also be required to be maintained in controlled environment as IP. Placebo must be consumed according to the same procedures and guidelines as ZingiVir-H.

**Primary Efficacy Endpoint:**

The Odds of Ratio for Improvement on a 7-point Ordinal Scale on Day 15 [Time Frame: Day 15 from the day of study inclusion]. The odds ratio represents the odds of improvement in the ordinal scale between the treatment groups. The ordinal scale is an assessment of the clinical status at a given day. Each day, the worst score from the previous day will be recorded.

The scale is as follows: 1. Death 2. Hospitalized, on invasive mechanical ventilation or Extracorporeal Membrane Oxygenation (ECMO) 3. Hospitalized, on non-invasive ventilation or high flow oxygen devices 4. Hospitalized, requiring low flow supplemental oxygen 5. Hospitalized, not requiring supplemental oxygen - requiring ongoing medical care (Coronavirus (COVID-19) related or otherwise) 6. Hospitalized, not requiring supplemental oxygen - no longer required ongoing medical care (other than per protocol ZingiVir-H administration) 7. Discharge from hospital.

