**Subject Eligibility Criteria**

**Inclusion Criteria**

This study targets infectious subjects normally associated with treatment in hospital setting. The following main criteria for inclusion must be met for study entry:

1. Patients of both sexes aged from 18 years to 60 years old.
2. Willing and able to provide written informed consent prior to performing study procedures by the subject or legal guardian willing and able to provide written informed consent prior to performing study procedures
3. Patients with Severe Acute Respiratory Syndrome Coronavirus (SARS-CoV)-2 infection confirmed by RT Polymerase chain reaction (RT-PCR) test between 1 and 120 Hours before randomization
4. Currently hospitalized and requiring medical care for COVID-19
5. Peripheral capillary oxygen saturation (SpO2) > 94% on room air at screening
6. Radiographic evidence of pulmonary infiltrates

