**Blinding**

Study drug will be assigned and administered in a Single blind fashion.

In the event of a medical emergency where it is imperative to know which treatment arm the subject was randomized to in order to make future treatment decisions, the Investigator may break the blind for an individual subject after getting approval from study monitor or sponsor. If any adverse events causing the need for subject unblinding, will be handled as a serious adverse event in accordance with the procedures outlined in this protocol. Any broken blind will need to be clearly justified, explained by a comment within the Case Report Form (CRF), and captured on the Serious Adverse Event Form.

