**Ordinal Scale assessment: Day 01 to EOT & EOS**

Ordinal Scale on the Odds of Ratio of Improvement on a 7-point scale between the treatment groups. The ordinal scale is an assessment of the clinical status will be assessed and documented on daily basis from Day-01 to EOT and on EOS. Each day, the worst score from the previous day will be recorded in the CRF.

The scale is as follows: 1. Death 2. Hospitalized, on invasive mechanical ventilation or Extracorporeal Membrane Oxygenation (ECMO) 3. Hospitalized, on non-invasive ventilation or high flow oxygen devices 4. Hospitalized, requiring low flow supplemental oxygen 5. Hospitalized, not requiring supplemental oxygen - requiring ongoing medical care (Coronavirus (COVID-19) related or otherwise) 6. Hospitalized, not requiring supplemental oxygen - no longer required ongoing medical care (other than per protocol ZingiVir-H administration) 7. Discharge from hospital.

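### Score 6 of the primary ordinal scale exempts only ZingiVir-H tablets from ongoing medical care and leaves placebo tablets out, so a scorer who knows the arm could score identical inpatients differently

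*Protocol*

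**What the plan says.** The Protocol Synopsis, under Primary Efficacy Endpoint, sets the primary measure as "The Odds of Ratio for Improvement on a 7-point Ordinal Scale on Day 15". Two adjacent categories matter here, both for inpatients without supplemental oxygen:

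- Score 5: "requiring ongoing medical care (Coronavirus (COVID-19) related or otherwise").
- Score 6: "no longer required ongoing medical care (other than per protocol ZingiVir-H administration").

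The section Ordinal Scale assessment: Day 01 to EOT & EOS repeats the wording: "no longer required ongoing medical care (other than per protocol ZingiVir-H administration) 7. Discharge from hospital". Neither statement mentions placebo or uses a neutral term for the study tablets.

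The control arm takes tablets too. The Masking section says "Placebo must be consumed according to the same procedures and guidelines as ZingiVir-H", and Overall Study Design gives both arms the same six daily times for 10 to 15 days.

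On who may know the arm, the protocol gives more than one account. Both Masking sections list participant, care provider, investigator and outcomes assessor as masked. The title and Overall Study Design say single blinded, and the Blinding section says "Study drug will be assigned and administered in a Single blind fashion". Overall Study Design also leaves allocation to the investigator's discretion.

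**The concern.** The exemption in score 6 exists so that taking trial tablets does not by itself keep a recovered inpatient in score 5. As worded, it does this for one product only. Score 5 is broad, since it covers any ongoing care whether or not it is related to COVID-19. A placebo patient whose only remaining care is the tablets is therefore not protected by the text.

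The boundary matters because of who is enrolled. Entrants must be "Currently hospitalized and requiring medical care for COVID-19" and have "Peripheral capillary oxygen saturation (SpO2) > 94% on room air at screening". Together these describe score 5 at baseline, so the move from 5 to 6 is probably the first step that could count as improvement.

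At stake is a scoring difference in the primary endpoint that depends on the product taken and not on the patient's condition. If applied literally with the arm known, it can run only towards ZingiVir-H.

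**Working it through.** **Step 1. The text.** Take two inpatients off oxygen, alike in every respect, whose only remaining care is study tablets.

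| Scorer | Patient on ZingiVir-H | Patient on placebo |
|---|---|---|
| Knows the arm, reads literally | 6 | can be scored 5 |
| Knows the arm, reads the exemption as all study tablets | 6 | 6 |
| Does not know the arm | one rule for both | one rule for both |

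Only the first row separates the arms.

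**Step 2. Who is exposed.** Discharged patients score 7 in either arm. Patients who stopped tablets after the 10-day minimum need no exemption. That leaves patients still in hospital, needing no other care and still on tablets when the Day 15 score is set. The scale records the worst score of the previous day, so the Day 15 entry reflects Day 14, which lies inside the dosing window. The group can exist, but the protocol gives no figure for its size.

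**Step 3. Illustration of size.** The protocol gives no outcome distribution, so every input here is an assumption. Both arms have the same true Day 15 distribution: 10% at score 4 or below, 20% at score 5, *s* at score 6, and the rest at score 7, so that 70% are at 6 or 7. All patients at score 6 are taken to be still on tablets. A fraction *f* of the placebo 6s is recorded as 5.

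Dichotomised at 6 or better:

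OR = (0.70/0.30) / [(0.70 − *fs*)/(0.30 + *fs*)]

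- *s* = 20%, *f* = 100%: (70/30)/(50/50) = 2.33
- *s* = 20%, *f* = 50%: (70/30)/(60/40) = 1.56
- *s* = 20%, *f* = 25%: (70/30)/(65/35) = 1.26
- *s* = 5%, *f* = 100%: (70/30)/(65/35) = 1.26
- *s* = 5%, *f* = 50%: (70/30)/(67.5/32.5) = 1.12
- *s* = 5%, *f* = 25%: (70/30)/(68.75/31.25) = 1.06

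The alternative is a common odds ratio over the whole scale, from a maximum-likelihood proportional-odds fit to the same two distributions with scores 1 to 4 collapsed:

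| Share at score 6 | *f* | OR, cut at 6 | OR, proportional odds |
|---|---|---|---|
| 20% | 100% | 2.33 | 1.33 |
| 20% | 50% | 1.56 | 1.15 |
| 20% | 25% | 1.26 | 1.07 |
| 5% | 100% | 1.26 | 1.05 |
| 5% | 50% | 1.12 | 1.03 |
| 5% | 25% | 1.06 | 1.01 |

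The true odds ratio is 1 in every row. The common odds ratio is smaller because the misscoring moves only one of the cut points.

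**Step 4. Effect on the test.** Take the 100 evaluable subjects as 50 per arm, a cut at 6, 70% truly at 6 or 7, and a two-sided 5% level (the protocol does not state sidedness). By the normal approximation, moving 5%, 10% or 20% of the whole placebo arm from 6 to 5 gives a chance of 7.7%, 18.0% or 53.3% of a significant result favouring ZingiVir-H. The nominal chance is 2.5%. The protocol names Fisher's exact test, which is more conservative, so these are rough figures.

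**The case against.** The strongest reply is that this is loose drafting and not a scoring rule that depends on treatment. One scale is printed for all subjects. To put a placebo patient at 5, a scorer must count taking inert tablets as required medical care while not counting the identical ZingiVir-H routine. The instruction that placebo follows the same procedures supports treating the two alike, and many scorers would do so. This stands, and it lowers the probability of harm. It does not change the text, which names one product.

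The second reply is masking. A masked assessor cannot score by arm, so the most the wording could do is cause scorers to differ among themselves, without favouring either arm. This also stands, as far as masking holds. A reader might infer from the single-blind statement that the investigator is meant to know the arm. The protocol does not support that: the same Blinding section requires approval from the study monitor or sponsor before the investigator may break the blind, and both Masking sections list the investigator and the outcomes assessor as masked. What can be said is narrower. The masking statements conflict, and allocation at the investigator's discretion makes it doubtful that the arm stays hidden.

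Third, a reader might infer that the 5/6 boundary defines improvement, and so take 2.33 as the size of the bias. No section defines improvement by a cut or a number of points; the boundary's role is inferred from the inclusion criteria. The value 2.33 is the top of the range shown and needs a cut at 6, 20% of each arm at score 6 and still on tablets, and every one of the placebo 6s misscored.

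**Conclusion.** The point holds as a defect of wording in the primary endpoint. Score 6 exempts one arm's tablets by name and not the other's, and no section of the protocol corrects this. Bias towards ZingiVir-H needs three things together: a scorer who knows the arm, a literal reading, and an appreciable group still in hospital and on tablets when the Day 15 score is set. The protocol does not securely exclude the first and is silent on the size of the third.

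Under the stated assumptions the spurious odds ratio runs from 1.01 (5% at score 6, a quarter of placebo 6s misscored, proportional odds) to 2.33 (20% at score 6, all misscored, cut at 6). None of these values can be read from the protocol as the expected bias. Severity is low to moderate: the likely effect is small, but it sits in the definition of the primary endpoint and is easily removed.

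**What to change.** In the Synopsis (Primary Efficacy Endpoint), in Ordinal Scale assessment: Day 01 to EOT & EOS, and on the CRF score sheet, change the exemption in score 6 to: *(other than per-protocol study tablets, ZingiVir-H or placebo)*. Naming both products is clearer than the term study drug, which the Investigational Product section uses for ZingiVir-H itself.

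The cost is one phrase in two sections and on the CRF. The sample size, treatment and schedule are unaffected. The change should be made before scoring starts; if scoring has begun, 5/6 entries for inpatients on tablets should be checked against source without knowledge of the arm. The conflicting masking and allocation statements need to be reconciled separately; the neutral wording removes this particular problem whichever statement is kept.

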**Secondary Efficacy Endpoint:**

- Proportion of Participants experiencing Treatment-Emergent Adverse Events [Time Frame: First dose date up to 15 days]
- Changes in Haematological and Biochemical parameter like CBC,ESR, CRP, Troponin, Liver function test, Renal function test, [Time Frame: First dose date up to 15 days]
- Changes in inflammatory markers - IL2, IL6, Interferon α, IgG, IgM
- Significant changes in the Chest X-Ray before and after treatment.

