**Primary Safety Endpoints:**

- Serious Adverse Events
- Adverse Events
- Respiratory failure (Hypercapnic)

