**INVESTIGATIONAL PLAN**

**Overall Study Design**

This is a Randomized controlled, single blinded multi-center, comparative study of ZingiVir-H as an adjuvant therapy in hospitalized adults diagnosed with coronavirus disease 2019 (COVID-19). At inclusion, subjects who meet all inclusion criteria and no exclusion criteria will be assigned, in either therapeutic arm (ZingiVir-H), to receive ZingiVir-H in a dose of 500 mg tablet each consumed once in 3 hours ±1 hour between 6 AM and 9 PM in a given day (6AM, 9AM, 12Noon, 3PM, 6PM, 9PM) for a minimum duration of 10 days to Maximum 15 days OR will be on a Placebo arm to receive placebo (without active ingredients) each consumed once in 3 hours ±1 hour between 6 AM and 9 PM in a given day (6AM, 9AM, 12Noon, 3PM, 6PM, 9PM) for a minimum duration of 10 days to Maximum 15 days. The allocation of study arm is strictly as per the discretion of the Investigator. Whereas both the study groups shall be given standard of care of treatment as per the research site policies or COVID-19 therapeutic management policies. These doses will be administered orally. Blood samples for assessing CBC; safety laboratory tests and immunomodulatory markers will be obtained between baseline assessments (Day-01), during the day-06 of inclusion, at the end of the treatment day-15 and at the end of the study day-30. Safety-related assessments will include reports of adverse events and clinical laboratory test results.

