**Laboratory Samples**

Hospital laboratory can be used to access the following test. If the hospital laboratory has limitation an outside laboratory with NABL accreditations shall be arranged for sample analysis.

- Complete Blood Count with differential (Hemoglobin, Hematocrit, and WBC with differential count) & ESR – **Day-01, 06, EOT (Day15) & 30 of study period**
- Serum Chemistry- Creatinine, Urea, CRP, ALT, AST, Alkaline Phosphatase, Albumin, total bilirubin- **Day-01, Day 06 Only CRP, End of treatment- Day 10 OR Day 15, & End of study period Day 30**.
- Pregnancy test; Serum or Urine human Chorionic Gonadotropin (hCG) - Pregnancy test only required for woman of childbearing potential on the day of randomization (**Day-01**).
- Immunomodulatory markers, IL6, IL7, Interferon α, IgG, IgM- **Day 01, Day 06, End of treatment- Day 10 OR Day 15, & End of study period Day 30**.

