**End of Study visit (Day 30 ± 2 days) –Follow up**

- Changes in concomitant medications
- Adverse Events/Serious Adverse Events
- Vital signs
- Blood will be obtained for following laboratory tests once in 24 ±2 hours:
  - Complete Blood Count with differential (Hemoglobin, Hematocrit, and WBC with differential count) & ESR
  - Serum Chemistry- Creatinine, Urea, CRP, ALT, AST, Alkaline Phosphatase, Albumin, total bilirubin
  - Immunomodulatory markers, IL6, IL7, Interferon α, IgG, IgM

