**Serious Adverse Events**

Information about all serious adverse events (SAEs) will be collected and recorded on the SAE Report form within 24 hours of learning of its occurrence. A paper SAE form should be completed by the site and faxed or emailed to the sponsor within 24 hours using the safety reporting contact information provided. The site is to follow their local regulations related to the reporting of SAEs to their local IRB/IEC. An SAE is any undesirable sign, symptom, or medical condition which:

• Is fatal or life-threatening (i.e. an event with an outcome of ‘Death’), or

• Requires or prolongs inpatient hospitalization, or

• Results in persistent or significant disability/incapacity, or

• Constitutes a congenital anomaly or a birth defect; or

• Is medically significant, as determined by a qualified health professional, may jeopardize the subject, and may require medical or surgical intervention to prevent one of the outcomes listed above

• Major respiratory failure as per ICD-10

• Any adverse event causing the need for unblinding will be handled as a serious adverse event.

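### The adverse-event proportion and laboratory-change endpoints stop at Day 15 and are filed under efficacy, although the data run to Day 30; the serious-event definition and Day 06 chemistry also need correcting

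*Protocol*

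**What the plan says.** **Objective.** The Protocol's primary objectives, in the synopsis and again under Study Objectives, include "To determine the safety of ZingiVir-H in this test population". No time frame is attached.

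**Endpoints.** Under Secondary Efficacy Endpoint the synopsis lists "Proportion of Participants experiencing Treatment-Emergent Adverse Events [Time Frame: First dose date up to 15 days". The next item covers changes in blood count, ESR and CRP, and continues "Troponin, Liver function test, Renal function test, [Time Frame: First dose date up to 15 days". The heading that follows, "Primary Safety Endpoints", lists serious adverse events, adverse events and hypercapnic respiratory failure, again with no time frame.

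**Collection.** Dosing lasts 10 to 15 days, with follow-up on Day 30 (Duration of Treatment). The End of Study visit at Day 30 ± 2 lists "Adverse Events/Serious Adverse Events", blood count with ESR, and chemistry including creatinine, urea, ALT, AST and bilirubin. Laboratory Samples also schedules these tests on Day 30.

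**Serious events.** The first criterion under Serious Adverse Events reads "Is fatal or life-threatening (i.e. an event with an outcome of" death.

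**Day 06.** Overall Study Design says "Blood samples for assessing CBC; safety laboratory tests and immunomodulatory markers will be obtained between baseline assessments (Day-01), during the day-06 of inclusion". For serum chemistry, Laboratory Samples gives "Day-01, Day 06 Only CRP, End of treatment- Day 10 OR Day 15", and the daily assessment visit names only ESR and CRP as Day 06 chemistry.

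**The concern.** The only adverse-event measure that has both a summary statistic (a proportion of participants) and a window ends when dosing may still be going on. The protocol's own reassurance about the mercury and arsenic compounds concerns cumulative dose over at most 15 days, so the window closes when cumulative exposure is highest. An effect that first appears later would be recorded at Day 30 but would not enter this measure. For laboratory changes no other endpoint is stated.

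The serious-event wording matters for a different reason. If life-threatening is read as fatal, a life-threatening event that the patient survives fails that criterion. Whether it is then reported to the sponsor within 24 hours depends on other criteria, one of which is a matter of professional judgment. With up to five sites, that invites inconsistent classification.

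The Day 06 conflict decides whether any renal or hepatic value is taken between baseline and end of treatment.

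**Working it through.** The protocol gives no figure for expected harms, so most of the check sets sections side by side. The little arithmetic there is concerns the window.

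**1. Endpoint lists against the visit schedule**

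| Item | Window in the endpoint list | Collected at Day 30? |
|---|---|---|
| Proportion with treatment-emergent adverse events (Secondary Efficacy Endpoint) | first dose to 15 days | yes |
| Haematology, liver and renal changes (Secondary Efficacy Endpoint) | first dose to 15 days | yes, except troponin, which no visit lists |
| Serious adverse events and adverse events (Primary Safety Endpoints) | none stated | yes |

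Adverse events therefore appear twice: once as a primary safety endpoint without a limit, and once as a secondary efficacy endpoint limited to 15 days. Nothing says which governs. Laboratory changes appear only in the limited form.

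**2. Post-dosing time inside the window.** A patient dosed for 15 days has 15 − 15 = 0 days after dosing within the window. A patient who stops at 10 days has 15 − 10 = 5.

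**3. Follow-up outside the window.** Share = (end − 15)/end.

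- Visit on Day 28: 13/28 = 46%
- Visit on Day 30: 15/30 = 50%
- Visit on Day 32: 17/32 = 53%

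**4. Events outside the window.** The documents give no onset pattern, so the following patterns are assumptions. If the onset rate halves every h days, let x = 2^(−15/h). The share of Day 1–30 events that fall after Day 15 is (x − x²)/(1 − x²) = x/(1 + x).

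- h = 3: x = 0.031, share 3%
- h = 7: x = 0.226, share about 18.5%
- h = 15: x = 0.5, share 33%
- constant rate: share 50%

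**5. Serious-event criterion.** The abbreviation i.e. makes what follows a definition, so the criterion shrinks to fatal events. The Adverse Events section grades severity up to a potentially life-threatening Grade 4, so the protocol elsewhere recognises such events in survivors. The remaining serious criteria are hospitalization, disability, congenital anomaly, medical significance, major respiratory failure and need for unblinding.

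**6. Day 06.** Overall Study Design places safety laboratory tests on that day. Laboratory Samples limits Day 06 chemistry to CRP, and the daily assessment visit to ESR and CRP. Under these two sections no renal or hepatic test is scheduled between Day 01 and end of treatment. The three sections agree on blood count and immune markers.

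**The case against.** A reader might infer that safety assessment closes at Day 15, that harms are therefore under-counted, and that the comparison leans toward no harm. The documents do not support this. The Primary Safety Endpoints have no time limit, and adverse events are recorded at Day 30, so an event on Day 20 is both seen and eligible for a stated endpoint. The Adverse Events section also counts clinically significant worsening of laboratory values after baseline as an adverse event, so a bad Day 30 result can enter by that route. The 15-day window applies to both arms alike. It can lose sensitivity to late effects, but a bias would need an onset pattern that is nowhere given. A summary limited to the treatment period is also a legitimate choice in itself.

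A reader might also put the loss in terms of detection. With 112/2 = 56 treated patients and an assumed 30-day risk of 5% with even onset, the chance of at least one event is 1 − 0.95^56 = 94% by Day 30 and 1 − 0.975^56 = 76% by Day 15. The arithmetic is right, but it rests on one assumed risk and the least favourable of the onset patterns above. With 18.5% of events late, the risk by Day 15 is 0.05 × 0.815 = 0.041 and the chance is about 90%. These figures also describe one arm, not a treatment comparison, and an event after Day 15 is still recorded.

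On serious events, prolonged hospitalization, medical significance and major respiratory failure can still capture many survived life-threatening events, and no event leaves the adverse-event count. On Day 06, the design section speaks only generally of safety tests, the two detailed sections agree on leaving out renal and hepatic tests, and those tests remain scheduled at baseline, end of treatment and Day 30.

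All of this stands, and it limits the consequence. It does not settle which adverse-event window governs, give Day 30 blood count and chemistry a place in a laboratory-change endpoint, or make the serious-event definition correct.

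**Conclusion.** The point holds as a set of defects in the protocol's own text. The two Day 15 endpoints are filed under efficacy, conflict with the unlimited primary safety endpoints, and leave Day 30 blood count and chemistry outside any stated laboratory-change endpoint. The serious-event definition reduces life-threatening to fatal. The Day 06 chemistry statements disagree.

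The consequence is possible rather than shown: late harms could be under-reported and serious events classified inconsistently. About half of follow-up time (46% to 53% over the visit window) lies outside the two endpoints. The share of events that this represents cannot be derived from the protocol and ranges from about 3% to 50% on the assumed patterns. The correction should be made, chiefly because the serious-event wording is a reporting rule that bears on patient safety and because the Day 30 data are already being collected.

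**What to change.** 1. **Synopsis endpoints.** Move the treatment-emergent adverse-event proportion and the laboratory changes from Secondary Efficacy Endpoint to the safety endpoints, and align them with the adverse-event entry there. Set the window as first dose to the Day 30 ± 2 visit, and keep Day 15 as an additional summary. Since no visit lists troponin, the endpoint and the schedule must be brought into agreement on it.
2. **Serious Adverse Events.** Delete the parenthesis that explains life-threatening by death, so that fatal and life-threatening are separate criteria.
3. **Day 06.** Reconcile Overall Study Design with Laboratory Samples and the daily assessment visit on which chemistry is taken. This review does not say which version is right.

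The first two changes need no new visit, and extending the window needs no new sample. They cost a longer summary table and possibly less favourable event counts. Some more events may need reporting as serious within 24 hours.
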